##### Treatment and evaluation phase

Both the treatment and placebo-control groups will be hospitalised for 4 days, and after a washout period of over 4 weeks the participants will be hospitalised again for 4 days. During hospitalisation, subjects will be administered GJD or placebo (one pill twice a day 30 min before breakfast and dinner) for 3 days. Group A participants will be administered GJD in phase I, followed by placebo treatment in phase II (both treatments will be administered twice daily for 3 days each). Group B participants will be administered placebo in phase I, followed by GJD treatment in phase II (same regimen as in group A; Fig. 1). To assess the effects of GJD treatment, participants will be allowed to sleep for only 4 h (02:00 to 06:00) on days 2 and 3 to artificially induce fatigue, and will carry out various activities such as walking, taking lectures, and watching movies to limit daytime sleep. To control possible bias, all subjects will be limited to intensive exercise and will consume the same foods during the study periods.

**Fig. 1 Fig1:**
[figure not shown]
Flowchart describing the study plan

Blood samples will be collected at 06:30 for analysis of serum cortisol, stress hormones, oxidative stress-related biomarkers, homocysteine, and immunological factors. Saliva samples will be collected at 06:30, 12:00, and 21:00 for analysis of salivary cortisol, while HRV will be assessed at 15:00–17:00. Self-reporting of FSS-K, BFI-K, KMLSEQ, and daily fatigue and sleep status will be carried out via questionnaires after dinner on days 1, 2, 3, and 4.

After a 4-week washout period, participants will be admitted to phase II for 4 days, during which they will undergo the same schedule.

The schedule of events for the trial is outlined in Table 1 and the study participants’ timeline of activities, treatments, and assessments during hospitalisation is shown in Fig. 2.

**Table 1 Tab1:**
[figure not shown]
Schedule of treatments and outcome measurements

^a^Stress hormones; oxidative stress-related biomarkers: serum cortisol, epinephrine, norepinephrine; ROS, NO, MDA, protein carbonyl, GSH, GSH-Rx, SOD, catalase, TAC

^b^Immunological factors: TNF-α, IFN-γ, IL-2, IL-10, IL-12, T cell, B cell, NK cell

● Evaluation at any time; ○ 06:30 (30 min after waking up); ◎ 06:30 (30 min after waking up), 12:00 (before lunch), and 21:00; □ 15:00–17:00 (before dinner); ▣ 07:30–08:30, 12:10–13:00, and 17:30–18:30; ■ 18:30–21:00 (after dinner); ◈ 1 pill twice a day, 30 min before breakfast/dinner

**Fig. 2 Fig2:**
[figure not shown]
Timeline of participant activities, treatments, and assessments during each study phase

### Study participants

#### Inclusion criteria

Participants are eligible for inclusion in the study if they meet the following criteria:Healthy male volunteers aged 19 to 45 years at the screening visitParticipants must weigh over 45 kg, with a body mass index of 18.5–30 kg/m^2^ at the screening visitParticipants must not have any congenital defects or chronic diseases that have been present within the 3 years prior to the screening visit and should have no pathological or abnormal clinical findings on physical examinationParticipants must not have any sleep disorders and must have Pittsburgh Sleep Quality Index (Korean version; PSQI-K) scores of 5 points or lowerParticipant must keep normal nocturnal sleeping hours (between 21:00 and 09:00) for a week before the first administration of the investigational drug (or placebo)Participants must sleep at least 7 h per night for a week before the first administration of the investigational drug (or placebo)Participants must be nonsmokers or ex-smokers who stopped smoking at least 1 year before the screening visitParticipants must comprehend the purpose and process of the study as well as the properties of the investigational drug and must voluntarily sign a written informed consent approved by the Institutional Review Board of Daejeon Korean Medicine Hospital of Daejeon University

#### Exclusion criteria

Participants who experience, have, or have had one or more of the following will be excluded:A clinically significant medical history or a current disease in one of the following areas: cardiovascular, respiratory, gastrointestinal, hepatic, metabolic and endocrine, renal and urinary, reproductive, musculoskeletal, skin and connective tissue, neurological, psychiatric, or allergic (other than seasonal allergies that are asymptomatic at the screening visit) diseaseA medical history of gastrointestinal diseases (oesophageal achalasia, oesophageal stricture, or Crohn’s disease) or operations (other than simple appendectomy or hernia surgeries) that may affect drug absorptionLaboratory test results showing alanine aminotransferase (ALT) or aspartate aminotransferase (AST) levels of more than twice the upper limit of the normal rangeA history of alcohol or drug abuse within the 12 months before the screening visitHistory of regular alcohol consumption (>210 g/week) within the 6 months before the screening visit. (Beer (5 % v/v): 250 mL = 10 g, *soju* (20 % v/v): 50 mL = 8 g, wine (12 % v/v): 125 mL = 12 g)Participation in another clinical study during the 2 months before the screening visitTreatment with drugs with known effects on drug-metabolising enzymes (e.g. dexamethasone, phenytoin, carbamazepine, rifabutin, rifampicin, phenobarbital, ketoconazole, itraconazole, clarithromycin, atazanavir, indinavir, nelfinavir, ritonavir, clarithromycin, telithromycin, voriconazole, etc.) during the 30 days before the screening visitWhole blood donation during the 2 months before the screening visit, or specific blood component donation in the month before the screening visitSeated systolic blood pressure ≥140 mmHg or diastolic blood pressure ≥90 mmHg at the screening visit Intake of prescribed or over-the-counter drugs during the 7 days before the first administration of the investigational drug (or placebo) Consumption of alcohol during the 7 days before the first administration of the investigational drug (or placebo) Serious, acute, or chronic medical or mental conditions or abnormal laboratory findings that may be exacerbated by administration of the investigational drug or participation in the study, or that may affect the study outcomes Hypersensitivity to the investigational drug or any of its components Absence of intention or ability to adhere to the behavioural rules and requirements as specified in the present protocol Any person considered unsuitable for participation in the study by the principal investigator

### Intervention

Trial medications will be prepared by Kyoung-Bang Pharmaceutical Co. Ltd. (Incheon, Republic of Korea) certified in Good Manufacturing Practices of herbal medicine extract pills and granules from the Ministry of Food and Drug Safety (MFDS). Quality control and quality assurance on the quality and safety testing, the packaging, and the contents of the treatment interventions including checks for potential contaminants, such as heavy metals or steroids, will be undertaken by the manufacturers to ensure treatment drug stability and quality.

Quality control and quality assurance regarding the identification of products as well as quality and safety testing will be conducted by the manufacturer. The raw herbs will be washed, dried, ground, and mixed with a pure form of honey (*Mel*) before being wrapped in gold foil and formed into pills. The pills will be packaged in identically shaped containers weighing 3.75 g each. The GJD and placebo pills will be formulated to a similar size, shape, taste, and flavour and will be wrapped in gold foil.

GJD consists of three medicinal herbs (*Ginseng radix*, Korean angelica, *Corni fructus*), two animal-derived materials (*Cornus cervi parvum* and *Moschus*) and *Mel*. All constituents of the formulation will comply with *Korean Pharmacopoeia* standards [40]. A placebo will be manufactured by the same pharmaceutical company and will be comprised of corn starch as the main ingredient, as well as small amounts of *Dioscoreae rhizoma*, *Poria sclerotium*, *Mel*, a colouring agent, and a flavouring agent. Each pill will weigh 3.75 g and the amounts and sources of each component of the formulation are shown in Table 2. The participants will take GJD or placebo twice a day 30 min before breakfast and dinner, a total of six times during hospitalisation.

**Table 2 Tab2:** Composition of *Gongjin-dan*

Herbal name		Scientific name (local name)	Quantity (g/pill)	Place of origin
Herbs	*Corni fructus*	*Cornus officinalis* Siebold et Zucc. (山茱萸)	0.9	Korea
	Korean angelica	*Angelica gigas* Nakai (當歸)	0.9	Korea
	*Ginseng radix*	*Panax ginseng* C.A. Meyer (人蔘)	0.9	Korea
Animal derives	*Moschus*	*Moschus moschiferus* L. (麝香)	0.15	Russia
	*Cornus cervi parvum*	*Cervus nippon* Temminck (鹿茸)	0.9	Russia
Diluting agents	*Mel*	*Apis indica* Radoszkowski (蜂蜜)		Korea
	*Aurum*	Gold (金)		Korea

During the study period, subjects will not be allowed to receive other fatigue-related treatments such as dietary supplements or alternatives. A practitioner will check to ensure that participants have taken the GJD or placebo immediately after administration and will collect empty bottles in order to confirm that all doses have been taken.

### Outcomes

Detailed outcome measurement time points are provided in Table 1.

#### Primary outcome

The primary outcome of this study is the participants’ serum cortisol levels. The effect of GJD on serum cortisol will be assessed by observing differences in cortisol levels before (day 2) and after (day 4) administration with GJD or placebo dosing after fatigue has been induced by sleep deprivation in healthy subjects. Considering circadian rhythms, cortisol will be measured at a specific time daily. Serum cortisol levels will be measured on an empty stomach 30 min after waking, and subjects will not eat foods that might affect cortisol levels, such as those high in sugar, fat, or protein for 12 h before the first administration of the investigational drug or placebo [12, 13].

#### Secondary outcome

Salivary cortisol levels, the secondary outcome of this study, will be measured once at admission on day 1 at 21:00, and three times daily on days 2–4; for example, cortisol will be measured within 30 min of waking, at 12:00, and at 21:00. Subjects will not eat within approximately 1 h or brush their teeth within 10 min before saliva collection in order to avoid contamination.

Blood samples for analysis of epinephrine, norepinephrine, oxidative stress-related biomarkers (reactive oxygen species (ROS), nitric oxide (NO), malondialdehyde (MDA), protein carbonyl, glutathione (GSH), GSH reductase (GSH-Rx), superoxide dismutase (SOD), catalase, and total antioxidant capacity (TAC)), homocysteine, and immunological factors (tumour necrosis factor (TNF)-α, interferon (IFN)-γ, interleukin (IL)-2, IL-10, IL-12, T cells, B cells, and natural killer (NK) cells) will be collected at the same time as the serum cortisol samples. Complete blood counts will be conducted to quantify the populations of T cells, B cells, and NK cells during phase II, day 2.

A self-reported questionnaire validated for each purpose and modified to a Korean version will be utilised to measure perceived fatigue. The FSS will be used to measure overall fatigue status [14], the BFI for variation in daily fatigue [15, 16], and the LSEQ for variation in sleep aspects [17]. The nine-item FSS is a self-reporting questionnaire developed by Krupp et al. [14] and serves to evaluate fatigue during the past week using statements that the participants must scale from 1 to 7 in terms of degree of agreement. The BFI is a self-reporting questionnaire developed by Mendoza et al. [15] to evaluate fatigue in patients with cancer. This nine-item questionnaire assesses the degree of fatigue at the present moment and for the past 24 h, as well as the impact of fatigue on daily life, on a scale of 0 to 10. The LSEQ consists of 10 items, each of which is measured on the Visual Analogue Scale (VAS); each item contains opposite statements at both extremes. The LSEQ involves four domains related to sleep: ease of initiating sleep (questions 1, 2, and 3), quality of sleep (questions 4 and 5), ease of waking (questions 6 and 7), and behaviour after waking (questions 8, 9, and 10). To complement the results of the BFI-K and the KMLSEQ, a daily sleep and fatigue status questionnaire developed by our research team will also be completed by the participants. This checks daily sleep and fatigue intuitively on the VAS and is structured so that participants can spontaneously describe a variety of their own symptoms.

In the afternoon of days 1–4, HRV testing will be performed to study variations in the autonomic nervous system responses relevant to fatigue, where HRV is measured as variations in the beat-to-beat intervals; R is a point corresponding to the peak of the QRS complex of the electrocardiogram (ECG) wave and RR is the interval between successive Rs. For HRV assessments, 5 min of ECG signalling will be measured and calculated using a Neo Dinamika system (MR Co. Ltd., Gyeonggi-do, Republic of Korea). The HRV measurements will be taken after participants rest for 10 min, and the subjects will be seated comfortably in a chair in a quiet and bright room at 20–25 °C for the assessment. The equipment will be connected to the medial side of both wrists and ankles as well as to the insides of both wrists and the right ankle. Rhythm parameters of the HRV include pulse rate, vegetative balance index, rhythm vegetative factor, regulation process adequacy index, and tension index. Vegetative regulation parameters of the HRV include regulation level and regulation reserves. Statistical analysis of the HRV includes the RRNN (mean of normal-to-normal (NN) intervals, which is all intervals between adjacent QRS complexes); the SDNN (standard deviation of NN intervals); CV (coefficient variation); the RMSSD (the root mean square of successive NN interval differences); the NN50 (the number of interval differences of successive NN intervals greater than 50 ms); and the pNN50 (the proportion of NN50 divided by total number of the mean of all normal NN intervals). Spectral analysis includes HF (high frequency, 0.15–0.4 Hz), LF (low frequency, 0.04–0.15 Hz), VLF (very low frequency, 0.0033 to 0.04 Hz), normalised HF, normalised LF, LF/HF ratio and TP (total power).

### Laboratory analysis

#### Determining stress hormones

Serum and salivary levels of cortisol as well as serum levels of norepinephrine and epinephrine will be assessed using enzyme-linked immunosorbent assay (ELISA) kits (LDN GmbH & Co., Nordhorn, Germany) according to the manufacturer’s protocol.

#### Determining oxidant biomarker levels in serum

Total serum levels of ROS will be determined according to the method described by Hayashi and colleagues [18]. Serum NO levels will be determined using the Griess method [19] and serum lipid peroxide levels will be determined using thiobarbituric acid (TBA) reactive substances as previously described [20]. The serum levels of protein carbonyl will be measured using a commercial ELISA kit (Cell Biolabs Inc., San Diego, CA, USA) and serum homocysteine levels will be analysed using an auto-analyser (AU400; Olympus, Tokyo, Japan).

#### Determining antioxidant biomarker levels in serum

Total antioxidant capacity (TAC) will be determined using a previously described method [21]. The serum levels of total glutathione (GSH) and GSH reductase (GSH-Rx) will be determined using commercial kits (Abcam, Cambridge, MA, USA) and SOD activity in the serum will be determined using an SOD assay kit (Dojindo Laboratories, Kumamoto, Japan) according to the manufacturer’s protocol. Serum catalase activities will be assayed as previously described [22].

#### Determining immune-related cytokine levels in serum

Serum levels of immune-related cytokines will be measured using commercial ELISA kits for TNF-α, IFN-γ as well as IL-2, IL-10, and IL-12 (BD Biosciences, San Jose, CA, USA). Absorbance will be measured with a spectrophotometer (Molecular Devices, Sunnyvale, CA, USA).

#### Flow cytometry and haematological analysis

Lymphocyte subclasses in the peripheral blood will be analysed using a BD Multitest IMK kit with a FACSCalibur instrument and Cell Quest Pro software (BD Biosciences, San Jose, CA, USA). Complete blood counts will be obtained using a Hemavet analyser (CDC Technologies, Dayton, OH, USA). T cells (CD3+), B cells (CD19+), and NK cells (CD3–/CD16+/CD56+) will be quantified as a percentage of the total number of lymphocytes.

### Randomisation and allocation concealment

Randomisation codes will be generated through block randomisation in a 1:1 code for groups A (phase I: GJD, phase II: placebo) and B (phase I: placebo, phase II: GJD). For the generation of a randomisation code, Random Allocation Software program v2.0.0 (M. Saghaei, MD, Department of Anaesthesia, Isfahan University of Medical Sciences, Isfahan, Iran) will be used.

### Blinding

A researcher who is not involved in recruitment or assessment will assign the clinical trial subjects identification numbers based on the randomisation code in order to avoid identifying groups. The number will be written on a piece of paper, put in a sealed envelope so that it is not visible, and stored in a double-locked cabinet. A researcher who is not involved in the generation of randomisation codes will open the envelopes sequentially and assign a clinical trial subject to each identification number. The opened envelope will also be stored separately in a double-locked cabinet. The clinical trial subjects will be informed that different medicines are given in phase I and phase II, but will not be told in which phase the therapeutic medicine is given. The process of attaching the randomisation code after manufacturing and packaging of GJD and placebo will be conducted by a researcher who is not involved in assessments to avoid breaking the blind. A researcher will provide medication immediately before each administration time and will check whether or not the subject takes the medication to avoid exchanging medicines between subjects during hospitalisation. To evaluate whether blinding of clinical trial subjects has been properly conducted, an assessment of blinding will be performed using a self-reported questionnaire developed by our research team at the end of the trial, at which point the subjects will be asked in which phase they perceived to have received the medication (as opposed to the placebo).

### Sample size

No previous clinical trials for serum cortisol levels from which sample size could be calculated have been reported; however, we consider a sample size of 24 to be a practical number for detection of clinically important differences between treatment and control groups. This number of subjects (12 per group) is the recommended minimum number per group for pilot studies [23]. We judged that this pilot study recommendation is applicable to feasibility study described here. Based on the results of this study, pilot trials will be needed in order to calculate appropriate sample size.

### Statistical analysis

An independent statistician who will be blinded to the randomised allocation for participants will carry out the statistical analyses. Measured variables including primary and secondary outcomes will be assessed using the full analysis set (FAS) based on intention-to-treat (ITT) principles. The per-protocol (PP) analysis set will be used for the sensitivity analysis. The baseline characteristics for both randomly allocated sequence groups are summarised by means and standard deviations for the continuous variables if satisfying the normal assumption, or median and interquartile range for nonnormal data. Normality will be tested by using the Shapiro-Wilk test. Frequencies and percentages will also be presented for categorical variables. The baseline difference between both sequence groups will be assessed using an independent two-sample *t* test or a Wilcoxon’s rank sum test for continuous variables, and the chi-squared test or Fisher’s exact test will be used to verify the randomised allocation for categorical variables.

Changes in serum cortisol levels between the baseline (day 2) and after treatment with GJD or placebo will be calculated to assess the primary outcome according to the following equations:$$ {C}_{GJD}={X}_{GJD(E)}-{X}_{GJD(BL)} $$$$ {C}_{PL}={X}_{PL(E)}-{X}_{PL(BL)} $$where *C* is the change in serum cortisol level, *X* is the serum cortisol level, *E* is the end point, *BL* is the baseline, *GJD* is *Gongjin*-*dan* treatment, and *PL* is placebo.

The primary outcome analysis (*Δ = D*_*GJD*_*– D*_*PL*_) will be performed in two stages. First, a linear mixed effect model will be applied to assess the effect of treatment, sequence, and period with the random effect for subjects. The carryover effect due to preceding the treatment stage will then be estimated by testing the effect of sequence in the model. The linear mixed model will be modified by confounding the sequence effect to the error term if the carryover effect is not significant. Otherwise, the model will be rebuilt based on data collected in the first phase of the study. An analysis of variance (ANOVA) table for the model will be provided and least square means and their standard errors (95 % confidence intervals) will be reported for each treatment. Second, if the structure of data is balanced and the carryover effect is invalid, simple paired two-sample *t* tests or Mann Whitney *U* tests will be performed to evaluate the effect of GJD. The results will be shown as means and standard deviations for each treatment group and mean differences between the two treatments (95 % confidence interval) will be reported.

The analysis of secondary outcomes will be focussed on changes of measures within each treatment group from the baseline to the end of study. Again, the linear mixed effect model will be applied. The level of significance will be set to 0.05 (two-tailed) and all analyses will be performed with PROC MIXED and PROC GLM in SAS software, version 9.4 (SAS Institute Inc., Cary, NC, USA).

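### The primary analysis subtracts day 2 cortisol with its weight fixed at 1; using it as a covariate is valid, needs no new data and is usually more precise, by an amount the article does not let one fix

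*Protocol article*

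**What the plan says.** The Primary outcome section compares "differences in cortisol levels before (day 2) and after (day 4) administration with GJD or placebo dosing". There is one serum value per morning: "Blood samples will be collected at 06:30 for analysis of serum cortisol" (Treatment and evaluation phase, text after Fig. 1). The Statistical analysis section gives the formula, end point minus baseline, separately under GJD and under placebo: "Changes in serum cortisol levels between the baseline (day 2) and after treatment with GJD or placebo will be calculated".

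In the primary model, "a linear mixed effect model will be applied to assess the effect of treatment, sequence, and period with the random effect for subjects". If the carryover test is significant, "the model will be rebuilt based on data collected in the first phase of the study". If the data are balanced and there is no carryover, "simple paired two-sample *t* tests or Mann Whitney *U* tests will be performed to evaluate the effect of GJD".

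At every step the day 2 value enters only by subtraction. The article writes out both the outcome formula and the model terms, so this choice is fixed and not left to a later document. Secondary outcomes are to be analysed as changes from baseline within each treatment group, again with a linear mixed model.

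**The concern.** In a parallel-group trial, a change score is attractive because it removes stable differences between people. In this crossover each participant serves as his own control, so the stable cortisol level already cancels between phases. A phase baseline can then help only through whatever day 2 and day 4 still share within a phase once the subject's own level is removed. Each is a single morning sample, two days apart, so that shared part may be small. If it is, subtracting the baseline adds more noise than it removes.

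What is at stake is precision, not validity. With 24 participants, the interval around the primary estimate could be wider than the collected data require.

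**Working it through.** **Inputs from the article.** 24 participants, 12 per sequence, allocated 1:1; two-sided 0.05; one serum value on day 2 and one on day 4 in each phase. The 24 is 2 × 12 from a cited minimum for pilot studies. No effect size, SD or power is given, so there is no calculation to reproduce.

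**Assumed, with ranges.** After the subject's stable level is removed, let r be the correlation of day 2 with day 4 within a phase, and k = baseline SD / end SD. The article gives neither.

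**Step 1: variance per subject.** Take phase I minus phase II differences and write s² for the within-subject variance of the end value.

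- Change score: 2s²(1 + k² − 2rk)
- End value alone: 2s²
- Baseline-adjusted: 2s²(1 − r²)

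**Step 2: ratios.** Change/adjusted = (1 + k² − 2rk)/(1 − r²) = 1 + (k − r)²/(1 − r²). This is never below 1 and equals 1 only when r = k, where the best weight, r/k, happens to be 1. Subtraction beats ignoring the baseline only if r > k/2. With equal variances (k = 1), the ratio is 2/(1 + r) and the threshold is 0.5.

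**Step 3: price of estimating the slope.** After intercept and sequence, 24 − 2 = 22 degrees of freedom remain. For normal data the adjusted variance is inflated on average by 1 + 1/(22 − 2) = 1.05, so the ratios are divided by 1.05.

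**Step 4: equal variances (k = 1).** Simulation used 20,000 trials per r. The last column is the power of the adjusted analysis at an effect for which the change score has about 76%. That effect is an illustration and not a property of this trial.

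| r | 2/(1+r) | divided by 1.05 | simulated, n = 24 | adjusted power |
|---|---|---|---|---|
| 0 | 2.00 | 1.90 | 1.90 | 96% |
| 0.3 | 1.54 | 1.47 | 1.46 | 90% |
| 0.5 | 1.33 | 1.27 | 1.26 | 86% |
| 0.7 | 1.18 | 1.12 | 1.13 | 81% |
| 0.9 | 1.05 | 1.00 | 1.00 | 76% |
| 0.95 | 1.03 | 0.98 | 0.97 | 75% |

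At r = 0.5 the adjusted/change variance ratio is 0.793, so the gain is worth 24/0.793, or about 30 participants. The adjusted estimate showed no bias.

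**Step 5: unequal variances.** Formula divided by 1.05, with simulated values (8,000 trials each) in brackets.

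| k | r = 0.3 | r = 0.5 | r = 0.7 |
|---|---|---|---|
| 0.5 | 0.99 (0.99) | 0.95 (0.95) | 1.03 (1.03) |
| 0.7 | 1.12 (1.12) | 1.00 (1.01) | 0.95 (0.95) |
| 1.3 | 2.00 (1.98) | 1.76 (1.79) | 1.62 (1.63) |

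The worst case is r = k, where the ratio is 1/1.05 = 0.95.

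**Step 6: phase I fallback.** For 12 against 12 with equal variances, the simulated change/adjusted ratios are 1.46, 1.27, 1.15 and 1.00 at correlations 0.3, 0.5, 0.7 and 0.9. Here nothing cancels between phases. The relevant correlation is the ordinary one across participants, which includes their stable differences and so may be higher.

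**Step 7: form of the covariate.** Adding only the raw phase baseline to the random-subject model gains less. Its adjusted/change ratio at r = 0.5 is 0.82 with between-subject variance equal to within-subject variance, and 0.885 with it three times as large. With the within-subject baseline difference the corresponding ratios are 0.80 and 0.79.

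**The case against.** The strongest objection is that nothing here is wrong. The change score is unbiased and answers the question that the Primary outcome section poses, and the Discussion says that the study is not powered for effectiveness. That stands: this is a gain in efficiency and not the correction of an error. It does not make the gain pointless, because the Sample size section still says "we consider a sample size of 24 to be a practical number for detection of clinically important differences" and the primary comparison is tested at 0.05.

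A second objection is that the size rests on quantities nobody has stated. This also stands. The 2/(1 + r) formula and the 0.5 threshold need equal variances. Day 4 follows restricted sleep, so equal spread cannot be presumed. A reader might infer that adjustment is free and always better; Step 5 shows a possible loss of about 5% at this sample size.

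A third objection concerns scope. A reader might infer that every secondary outcome loses precision in the same way. The article does not support that: salivary cortisol is sampled up to three times a day and the questionnaires are completed on all four days, so a calculation for one baseline and one end value does not carry over to them.

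Finally, changing the mixed model alone would leave the paired and rank tests, which have no place for a covariate, and the phase I fallback as they are. That is correct, and the fix has to cover them.

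**Conclusion.** The point holds as a recommendation on precision. The planned analysis is valid, but it imposes a baseline weight of 1 that the data could estimate. Under equal variances, the change-score variance at n = 24 exceeds the adjusted variance by a factor of about 1.9 to 2.0 at r = 0, 1.5 at 0.3, 1.3 at 0.5 and 1.1 at 0.7. The two break even near 0.9, and adjustment loses about 3% at 0.95. Under unequal variances the gain may be near zero, about 5% negative, or larger than these figures. The trade is favourable because the loss is bounded at roughly 5% while the possible gain is large.

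The article does not support saying that this trial will lose a large share of its information, since nothing shows that r is low.

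The conclusion also needs a day 2 value taken before the first dose. The Primary outcome section labels day 2 as before administration, but the contents of Table 1 are not available here to confirm the order of the 06:30 sample and the first dose.

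**What to change.** Before unblinding, prespecify the following:

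- **Primary analysis.** Model the end-of-phase (day 4) value with treatment, period and sequence as fixed effects and subject as random. Use as covariates that phase's pre-dose day 2 value and the subject's mean baseline over both phases. With complete data this is equivalent to regressing the between-phase difference in end values on sequence and the between-phase difference in baselines.
- **Carryover step.** State that the sequence term is then conditional on mean baseline, or say from which model the carryover test is taken.
- **Phase I fallback.** Use ANCOVA of the phase I end value on treatment and the phase I baseline.
- **Change scores and stage-two paired or rank tests.** Keep them as descriptive or supportive.
- **Secondary outcomes.** Apply the same adjustment only where a single pre-dose baseline is compared with a single end value.
- **Timing.** Confirm and state when the day 2 sample is taken relative to the first dose.

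The cost is one degree of freedom and the rewording of these analysis steps. No additional samples or visits are needed.
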